## Abstract

Introduction: Intermittent theta burst stimulation (iTBS) has been associated with improvements in the negative symptoms (NSs) of schizophrenia. However, optimizing by shorter protocols remains necessary. Furthermore, understanding their impact on other clinical symptoms, sleep, and autonomic regulation is important to underlying therapeutic effects. Objectives: Evaluate the efficacy of an accelerated iTBS protocol on reducing NSs in patients with schizophrenia. We hypothesize a 20% reduction in BNSS scores in the active group, as well as improvements in disorder-related aspects, including sleep patterns, symptoms severity, and cognition. Methods: A double-blind, randomized, sham-controlled clinical trial design will be conducted to test the effects of the accelerated iTBS protocol in 60 participants with schizophrenia (30 active and 30 sham) with moderate NSs. iTBS protocol will consist of four daily sessions, with 600 pulses per session for five consecutive days. Patients will be assessed at three time points (baseline, after intervention and 30 days follow up) for clinical symptoms, cognition and heart rate variability. The primary outcome will be negative symptoms using the Brief Negative Symptom Scale (BNSS). Study register: Brazilian Registry of Clinical Trials (CAEE: 71102823.4.0000.5505). Conclusions: The accelerated iTBS protocol has demonstrated promising effects on NSs. However, it is still necessary to establish an effective and feasible high-dosage protocol. This study will contribute to optimizing therapeutic protocols for schizophrenia, with a particular focus on clinical applicability. Additionally, it will provide an opportunity to deepen the understanding of the physiological effects of neuromodulation, contributing to the understanding of its underlying mechanisms.

## 1. Introduction

Schizophrenia is a mental disorder that affects approximately 0.4% of the population and is characterized by a complex and heterogeneous behavioral and cognitive syndrome, resulting from brain developmental abnormalities caused by the interaction of genetic risk factors and environmental exposures [1]. Despite its low prevalence, the disorder typically leads to substantial impairments related to quality of life, patient functionality, and prognosis, even with the best available treatments [2]. Although negative symptoms (NSs) are among the hallmark features of schizophrenia with significant clinical relevance, these symptoms present challenging for treatment and lack targeted therapeutic options. NSs are the primary predictor of low functionality and may be associated with impaired cognitive performance in these patients [3].

Neuromodulation techniques have emerged as promising alternatives for the treatment of negative symptoms. Non-invasive brain stimulation (NIBS) encompasses non-pharmacological techniques, either electrically or magnetically induced, that are frequently used in psychiatric disorders [4,5]. In this context, transcranial magnetic stimulation (TMS) has been distinguished as a technique that is capable of stimulating the cerebral cortex through a focal magnetic field, which induces an electrical current in the underlying brain tissue, promoting changes in cortical excitability and neuronal function [6,7]. In 2018, the FDA approved a new TMS modality, theta-burst stimulation (TBS), which delivers magnetic pulses in a specific “burst” pattern that can mimic endogenous theta rhythms, allowing treatments to be administered within a few minutes [8,9,10]. TBS protocols present significant advantages compared to traditional rTMS due to their shorter duration, enabling accelerated protocols in which multiple TBS sessions can be administered per day, delivering higher pulse doses within shorter periods with clinical safety and efficacy [4].

A recent meta-analysis that included 12 intervention studies using intermittent theta burst stimulation (iTBS) for negative symptoms showed that a higher total number of pulses, compared to relatively lower numbers of pulses, presents a greater effect size, suggesting that the efficacy of iTBS treatment is dose-dependent [11]. Definitions of parameters such as intensity, frequency, duration, waveform, and stimulation site need to be better defined. In this regard, accelerated TMS (aTMS) protocols, characterized by two or more sessions of TMS in a single day, have emerged as an effective alternative and appear to be a viable strategy for reducing total treatment time; it enables a greater number of sessions per day and delivers the same number of pulses and sessions of a conventional 6-week treatment within a single week, sometimes with efficacy surpassing that of daily session doses [12,13,14]. Despite its potential, the literature about the use of intermittent theta burst stimulation (iTBS) for treating negative symptoms of schizophrenia is still limited, especially regarding the type of protocol and the brain area to be stimulated, although the left dorsolateral prefrontal cortex (DLPFC) has shown promising results [15,16,17,18,19].

The studies conducted to date have limitations that hinder a better understanding of the true potential of intermittent theta burst stimulation (iTBS) for negative symptoms in schizophrenia, including the following: 1—few double-blind, randomized clinical trials; 2—small sample sizes; 3—the use of instruments that do not allow for the assessment of sub-domains of negative symptoms; 4—a lack of control for potential confounders in the evaluation of negative symptoms, such as depressive and extrapyramidal symptoms [15,16,17,20,21].

In addition to clinical improvement, the use of TMS has investigated the impact on physiological variables, among which is heart rate variability (HRV), a biomarker of autonomic nervous system activity and the brain–heart interaction through vagus nerve activity [22]. Physiological self-regulation is an adaptive process that is directly connected to volition and cognitive functioning in the general population [23], and it is shown to be reduced in various disorders [24], including schizophrenia [25], where dysregulation is observed regardless of antipsychotic use [26,27,28,29,30]. Research conducted with this population has not shown differences in blood pressure modulation and heart rate following rTMS; however, variables related to HRV associated with the fronto-vagal network were not analyzed [31].

Sleep disturbances are frequent in schizophrenia and go beyond pharmacological or psychotic-state effects. In patients with negative symptoms, they have been closely linked to clinical features of the disorder, including an association between an altered sleep architecture with prefrontal dysfunction, aggravating motivational deficits, social withdrawal, and cognitive impairments [32]. Autonomic nervous system dysregulation is reported in association with sleep disturbances in several pathologies [33,34], with hyperarousal states during sleep being associated with predominant sympathetic activity [33] and parasympathetic predominance being reported in association with some hypersomnia disorders [34].

In this context, a clinical trial using an accelerated iTBS protocol in the left dorsolateral prefrontal cortex (DLPFC) is necessary, considering the positive results from studies conducted with conventional high-frequency rTMS protocols and the fact that accelerated protocols using iTBS have been demonstrated to be more effective [35]. The primary objective of the study will be to evaluate the efficacy of an accelerated transcranial magnetic stimulation (theta-burst—iTBS) protocol on reducing negative symptoms in patients with schizophrenia through a double-blind, randomized, sham-controlled clinical trial. The protocol aims to provide a greater number of sessions in a short period of time while maintaining the feasibility of application. The study will include multimodal assessments, including clinical, neuropsychological, sleep, and HRV evaluations, in order to establish the mechanisms of stabilization of these symptoms. We hypothesize a 20% reduction in BNSS scores in the active group, as well as improvements in disorder-related aspects, including sleep patterns, symptom severity, and cognition.

## 2. Materials and Methods

Design: We proposed a randomized, double-blind, sham-controlled clinical trial to test the effects of the accelerated iTBS protocol in participants with schizophrenia with negative symptoms (CONSORT—Figure 1). The study is conducted in accordance with the Declaration of Helsinki and has been approved by the Research Ethics Committee of the Federal University of São Paulo (UNIFESP) as of 14 September 2023 and registered in The Brazilian Registry of Clinical Trials (ReBEC) (CAEE: 71102823.4.0000.5505).

*Participants*:

We will recruit 60 volunteers, aged between 18 and 50 years of both genders, who have been diagnosed with schizophrenia according to the criteria of the Diagnostic and Statistical Manual of Mental Disorders (DSM-5), through an evaluation conducted via the Structured Clinical Interview for DSM-5 (SCID-5) and who present negative symptoms of moderate intensity (score ≥ 20 on the BNSS). Participants must have stable medication use, with no changes in antipsychotics in the three months prior to inclusion, and must not be using medications that could lower the seizure threshold, except for antipsychotics. Additionally, participants should not have a history of substance dependence or alcohol use in the past four weeks. In the case of smokers, the number of cigarettes and the last use will be documented. Regarding neuromodulation, participants should not have undergone any brain stimulation protocols in the past year prior to study enrollment. All participants must sign the informed consent form to participate in the study.

Participants will be allocated into two groups (intervention and sham), with 30 subjects per group. The statistical power for the primary analysis with this sample size is estimated to be β = 0.82. This calculation assumes (1) the use of mixed linear regression models for hypothesis testing, which will assess the interaction between time (baseline vs. T1) and treatment (intervention vs. sham), (2) a moderate effect size (f = 0.38), and (3) a significance level of 5% (two-tailed).

Randomization will be conducted in blocks of 6 individuals, with permutation in the order and size of the blocks, generated by the website www.randomization.com (accessed on 1 September 2023) and managed by an assistant with no affiliation to the project. Allocation will be carried out using opaque, sealed, standardized envelopes, which will be numbered and assigned to each participant, opened after the individual has been included in the study. The assessing researchers and participants will remain unaware of the type of intervention administered until the study is completed. Protocol implementation will be the responsibility of a researcher who will not collect data and will not be involved in any other aspect of the study, except for protocol application, to ensure blinding.

Exclusion criteria include the following: individuals with comorbid diagnoses of depression or substance use disorder, as defined by the DSM-5, assessed by the SCID; patients who meet DSM-5 diagnostic criteria for organic brain mental disorder or intellectual disability; psychotic episodes or prominent positive symptoms (PANSS positive scale ≥ 20) during the protocol; clinically determined neurological disorders (e.g., epilepsy and a history of seizures or syncope, traumatic brain injury) or severe clinical conditions; the presence of metal implants, such as pacemakers, cochlear implants, implanted electrodes/stimulators, aneurysm clips/coils, stents, or any other criteria common to TMS protocols; any condition that prevents the participant from attending the 5 treatment days.

The study will be conducted at the Integrated Mental Health Care Center Hospital (CAISM) in São Paulo, Brazil.

*Procedures*:

Patients who agree to participate in the study will be included in the sample after signing the Informed Consent Form. The research will be conducted in three phases (Figure 1): Baseline (T0, week 1): During the initial assessment, screening will be performed to verify inclusion and exclusion criteria. Individuals meeting the study criteria will be randomized into the intervention or sham group and will undergo clinical evaluation, heart rate variability (HRV) assessment, and neuropsychological evaluation. Patients must demonstrate clinical stability over the past three months, maintaining a positive psychopathology that is at most moderate (less than or equal to 4 on the items for positive symptoms of the Positive and Negative Syndrome Scale (PANSS) and exhibiting moderate or more severe negative symptoms, defined by scores equal to or greater than 20 on the Brief Negative Symptom Assessment Scale (BNSS). In this phase, baseline HRV will be measured, randomization will be defined, and measurements of the skull cap will be conducted according to the International 10–20 System reference for electroencephalography. Thus, the F3 area (corresponding to the left DLPFC) will be identified using the Beam F3 measurement system [36]. Intensity will be defined by identifying the lowest visible motor response (hotspot), with single pulses on the motor cortex using the lowest power of the equipment, through an automatic measurement system. For this, electromyography, EMG Neuro emg micro-2, (Neurosoft, Ivanovo, Russia)^®^, will be used, with electrodes positioned on the right abductor pollicis brevis muscle. During this phase, the individual will undergo a Safety Inventory for transcranial magnetic stimulation in adults. Intervention and reassessment (T1, week 2): The individual will undergo the protocol, consisting of 20 (twenty) intermittent theta burst stimulation (iTBS) sessions, conducted in 4 daily sessions over 5 consecutive days, i.e., one iTBS session per hour. This protocol corresponds to the total number of sessions conducted by Bation and colleagues; however, it was executed in half the time [16]. The protocol will be conducted with the patient seated in a chair. The coil will be positioned tangentially and perpendicular to the scalp in the area previously marked on a cap. At the end of each treatment day, an Adverse Effects Scale will be used to assess the safety of the technique. Upon completion of the protocol, initial clinical evaluations will be reapplied in the following week, as well as the heart rate variability (HRV) assessment and neuropsychological evaluation. T2 (week 3)—Follow-up 30 days: All assessments will be reapplied 30 days after the intervention.

A pilot study will be conducted at the beginning of the project, in which 10 volunteers will undergo the entire research process in an active protocol, aimed at training the team, adjusting the logistics of the protocol and evaluations, and addressing any physical and psychological aspects related to the volunteers.

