Differences between the baseline, after intervention, and follow-up (T0, T1, and T2) for each measure will be tested using mixed-effects linear models. The treatment effect will be estimated through the interaction between the intervention group (intervention or sham) and the assessment time (T0, T1, and T2). Effect estimates will be presented as post-intervention mean differences, along with 95% confidence intervals, *p*-values, and Cohen’s d effect sizes (where 0.2 represents a small effect, 0.5 represents a moderate effect, and 0.8 represents a large effect). Random effects from repeated measures within each subject will be modeled according to the covariance structure that shows the lowest index based on the Akaike information criterion (AIC). The following covariates will be included in the models: the Calgary Depression Severity Scale score, as depressive symptoms may confound the assessment of negative symptoms and individuals with severe depression will be excluded from the sample; the total score of the Clinical Global Impression-Severity scale (CGI-S), since the severity of illness may influence treatment response; and the Generalized Anxiety Disorder 7-item scale (GAD-7), due to anxiety symptoms. For the various exploratory analyses conducted with the previously detailed secondary outcomes, the significance value will be corrected for multiple tests using Bonferroni criterion, with an alpha of 0.05 divided by the number of tests.

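### The sample-size statement calls f = 0.38 moderate, but it equals d = 0.76, close to the plan's own mark for a large effect; the 0.82 is correct for f = 0.38 but is labelled β instead of 1−β

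*Protocol article*

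**What the plan says.** The protocol article, section 2 (Participants), fixes the sample: "Participants will be allocated into two groups (intervention and sham), with 30 subjects per group". It then gives the power: "The statistical power for the primary analysis with this sample size is estimated to be β = 0.82". The test behind that figure is a mixed linear model, "which will assess the interaction between time (baseline vs. T1) and treatment (intervention vs. sham". The remaining assumptions are "2) a moderate effect size (f = 0.38), and (3) a significance level of 5% (two-tailed".

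Section 2.5 says that effects will be reported as post-intervention mean differences with Cohen's d. It also supplies the scale for reading d: 0.2 is small, and "0.5 represents a moderate effect, and 0.8 represents a large effect".

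The article does not convert f to d. It does not say which standard deviation f is expressed in, and it states no correlation between the baseline and T1 scores.

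**The concern.** Two statements in the same article disagree about what a moderate effect is. The sample-size paragraph applies the word to f = 0.38. Section 2.5 applies it to d = 0.5, which for two equal groups is f = 0.25. On that scale large is d = 0.8, or f = 0.40. So f = 0.38 is 0.02 below the large mark and 0.13 above the moderate mark.

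A reader who takes the paragraph at its word will believe that 30 per group gives 82% power for a moderate effect. If the trial is then null, that reader may conclude that a moderate benefit has been made unlikely, when the calculation supports that only for an effect that is nearly large.

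The symbol is a second slip in the same place. Conventionally β is the type II error, so power should be written 1−β.

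**Working it through.** **Inputs.** From section 2: n = 30 per group (N = 60), f = 0.38, two-sided α = 0.05, power 0.82, and a time (baseline, T1) × treatment interaction with 1 df. From section 2.5: d = 0.5 moderate, d = 0.8 large.

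**1. Convert f to d.** With two equal groups f = d/2, so d = 2 × 0.38 = 0.76.

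**2. Reproduce the stated power.** Noncentrality of the t test: d√(n/2) = 0.76 × √15 = 2.943, on 58 df. Equivalently, for the F test, λ = f²N = 0.1444 × 60 = 8.66 on (1, 58) df. Both give power 0.825, and the normal approximation gives 0.837. The stated 0.82 is reproduced.

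A two-occasion time × treatment interaction is the two-group comparison of change scores. The same λ and power therefore apply to the test that the article names, provided f is standardised by that test's own error SD.

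**3. Other readings of 0.38.**

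| Reading | Power |
|---|---|
| One-sided test, d = 0.76 | 0.897 |
| 0.38 taken as d | 0.304 |
| 0.38 taken as f² | 0.997 |
| Within-between parameterisation with a correlation multiplier, 2 time points | at least 0.984 for any correlation of 0 or more |

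None of these gives 0.82, so d = 0.76 in the units of step 2 is the working interpretation.

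**4. Power at the article's moderate mark, same standardiser.** d = 0.50 is f = 0.25, so λ = 0.0625 × 60 = 3.75 and power is 0.478. The smallest d with 80% power is 0.736, and with 82% power 0.755.

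**5. Power at d = 0.50 in post-intervention SD units.** Section 2.5 attaches its scale to post-intervention differences, so this reading is also possible. Assume equal SDs at baseline and T1, with correlation r. The SD of change is then SD_post × √(2(1−r)), so d_change = d_post / √(2(1−r)). The article gives no r, so the values below are assumptions.

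| Assumed r | d_change for d_post = 0.50 | Power, change analysis | Power, baseline-adjusted (ANCOVA-type) | d_post equal to d_change = 0.76 |
|---|---|---|---|---|
| 0.3 | 0.42 | 0.36 | 0.51 | 0.90 |
| 0.5 | 0.50 | 0.48 | 0.59 | 0.76 |
| 0.7 | 0.65 | 0.69 | 0.76 | 0.59 |
| 0.8 | 0.79 | 0.85 | 0.89 | 0.48 |

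At r = 0.5 the two standardisers coincide, and the 0.48 of step 4 returns.

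**The case against.** The strongest reply is that nothing has been miscalculated. The power is right for f = 0.38, and f is printed beside the adjective, so the assumption is disclosed. That stands: the fault lies in the label and the symbol, not in the arithmetic.

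A second reply is that 48% is not fixed by the article. If f refers to change scores and d to post-intervention scores, a correlation of 0.7 to 0.8 would make f = 0.38 equal to d_post of 0.59 to 0.48, which is about moderate in section 2.5's terms. That also stands as a limit on the 48%. It does not rescue the wording, because the article states no correlation and does not say which SD it uses, so a reader cannot tell that this is meant.

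A third reply is that 0.76 still lies below 0.8 and could be called moderate. But section 2.5 gives points rather than bands, and 0.76 is 0.04 from one point and 0.26 from the other.

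A reader might also infer more than the text supports:

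- *That the trial has 48% power and the 82% is false.* The two figures belong to different effect sizes, and the article claims 0.82 only for f = 0.38.
- *That power is really 18%.* The sentence says it is giving statistical power, so the β is a notation slip.
- *That 0.82 cannot belong to the named interaction.* Step 2 shows that it can.
- *That dropouts erode the figure.* Section 2.5 defines a dropout by missed treatment sessions, not by a missing T1 score, and the article gives no rate of missing T1 scores.
- *That f = 0.38 fails to follow from the 20% hypothesis* ("We hypothesize a 20% reduction in BNSS scores in the active group"). The article never says that f was derived from it, and an SD and an expected sham change are details that an article may leave to the full protocol.

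**Conclusion.** Wrong as written; severity minor to moderate. The sample-size paragraph describes as moderate an effect that converts to d = 0.76, close to the article's own large mark, and it labels power as β. The 0.82 itself is correct for f = 0.38.

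For an effect at the article's moderate mark, power is about 0.48 when d has the same standardiser as f. When d is in post-intervention SD units and change is analysed, it is about 0.36 to 0.85 over assumed correlations of 0.3 to 0.8. The conversion to d = 0.76 needs only two equal groups. The 0.48 needs the common standardiser, and the range needs the assumed correlations and equal SDs at the two visits.

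This does not show that 60 participants is the wrong number. It shows that the claim attached to that number is worded more favourably than the calculation supports.

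**What to change.** Keep n = 60 and replace the power statement in section 2 with wording such as:

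> With 30 participants per group and a two-sided significance level of 5%, power (1−β) is 0.82 for f = 0.38, that is d = 0.76 (near-large), standardised by [the SD of T0–T1 change, or whichever SD was used]. The smallest d detectable with 80% power is 0.74. On the same standardiser, power at d = 0.50 is 0.48.

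Delete the word moderate from that sentence. The authors must fill in the SD from their own calculation. If it differs from the SD that will be used for Cohen's d in section 2.5, one further sentence should say so and give the assumed baseline-to-T1 correlation, so that the two scales can be compared.

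The cost is wording only: the sample size, test and analysis are unchanged. The one drawback for the authors is that the stated power looks less favourable.

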### 2.5. Statistical Analysis

The effects of the intervention will be analyzed according to the intention-to-treat (ITT) paradigm, which assesses the effect on all participants, regardless of their level of adherence to the treatment. The primary outcome of the study will be the reduction of negative symptoms, measured by the total score of the Brief Negative Symptom Scale (BNSS) with a score ≥20, while the secondary outcomes will focus on the reduction of negative symptoms as assessed by the negative symptom subscale score of the Positive and Negative Syndrome Scale (PANSS), the sub-domains of BNSS and physiological variables, through HRV assessment, sleep alterations and their association with negative symptoms, assessed by Pittsburgh and Epworth scales, and cognitive assessment by the MATRICS.

Missing data during follow-up will be handled using the restricted maximum likelihood method in mixed-effects linear regression analyses, allowing for the use of all data regardless of whether a participant completes the study, consistent with ITT analysis.

Clinical and demographic differences between groups will be initially evaluated at baseline using the Chi-square test for categorical variables and Student’s *t*-test for independent samples in continuous variables. These same tests will also be employed to identify potential differences between participants who complete the study and those considered to be dropouts. A participant will be considered a dropout if they miss any of the intervention protocol sessions, resulting in a loss of four sessions of intermittent theta burst stimulation (iTBS). A significance level of *p* < 0.05 will be adopted in all statistical analyses.

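### An exclusion criterion dated to the treatment period acts after randomisation and is not reconciled with the intention-to-treat analysis

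*Protocol article*

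**What the plan says.** **Exclusion criteria (protocol article, section 2, Materials and Methods).** One of the listed exclusions is "psychotic episodes or prominent positive symptoms (PANSS positive scale ≥ 20) during the protocol".

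**Timing of eligibility and allocation (section 2, Procedures, T0).** "During the initial assessment, screening will be performed to verify inclusion and exclusion criteria". Then: "Individuals meeting the study criteria will be randomized into the intervention or sham group".

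**Treatment (section 2, Procedures, T1).** After randomisation: "The individual will undergo the protocol, consisting of 20 (twenty) intermittent theta burst stimulation (iTBS) sessions".

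**Baseline positive symptoms (section 2, Procedures, T0).** Patients must have been stable for three months, "maintaining a positive psychopathology that is at most moderate (less than or equal to 4 on the items for positive symptoms" of the PANSS).

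**Analysis (section 2.5, Statistical Analysis).** The analysis follows intention to treat, "which assesses the effect on all participants, regardless of their level of adherence to the treatment". Missing follow-up data are handled by restricted maximum likelihood in mixed models, which use all available data whether or not a participant completes.

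**The concern.** An exclusion criterion normally decides who may be randomised. This one is dated to a period that, in the article's own usage, begins after allocation. The event it names, psychotic worsening, is one that stimulation could make more or less likely. If the criterion is applied as an exclusion at that stage, the set of participants kept depends on a post-randomisation outcome, and the two arms can lose different kinds or numbers of people. The comparison is then no longer protected by randomisation, and the arm that loses more worsened participants tends to look better.

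Section 2.5 promises the opposite: everyone is analysed. A team following section 2 and a statistician following section 2.5 could handle the same participant differently. The mixed model does not settle this, because it can use only the assessments that were made, and the article gives no assessment path for someone who meets the criterion before finishing the sessions.

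**Working it through.** **1. Does the criterion act before or after allocation?**
- Eligibility is verified at T0, and those who qualify are randomised at T0.
- The Procedures use protocol for the 20 sessions at T1. Reassessment is likewise timed from completion of the protocol, and the dropout sentence in section 2.5 speaks of protocol sessions.
- Positive symptoms at entry already have their own limit, on the items.
- Read with the article's own vocabulary, the criterion can be met only after allocation. If protocol is taken to mean the whole study, it still covers the time after allocation. Only a reading as a loosely worded entry criterion avoids the conflict.

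**2. When could the PANSS threshold be checked?**
- Section 2.2 schedules the clinical scales, including PANSS, at T0, T1 and T2. The Procedures place the T1 assessments in the week after the sessions.
- No PANSS is therefore scheduled on the five treatment days. The first scheduled PANSS after allocation is in the same T1 assessment as the BNSS. Excluding on it would select participants on a measure taken alongside the primary outcome.

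**3. How do the two positive-symptom limits fit together?** The article does not give the number of items. Assuming seven:
- All items scored 3: 7 × 3 = 21, which is at or above 20.
- All items scored 4: 7 × 4 = 28.
- Both profiles satisfy the item limit. If only the item limit applies at T0 and the scale limit applies later, such a participant would meet the exclusion with no worsening.

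**4. The plan's power figure.** Inputs from section 2: N = 60, f = 0.38, two-sided 5%.
- λ = f² × N = 0.1444 × 60 = 8.66. A noncentral F test with 1 and 58 degrees of freedom gives power 0.825, against the stated 0.82. The figure reproduces.
- The corresponding standardised difference is d = 2f = 0.76.

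**5. What removal could do (illustration only).** The article gives no rate for this event. Assume that a fraction p of one arm of 30 is removed and that their BNSS is 1 SD worse than that arm's full mean, with the SD taken as the unit of d. The retained mean shifts by p/(1 − p):
- 1 of 30: 1/29 = 0.03 SD, or 4.5% of 0.76.
- 2 of 30: 2/28 = 0.07 SD, or 9.4% of 0.76.
- 3 of 30: 3/27 = 0.11 SD, or 14.6% of 0.76.

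The shift is zero if BNSS in those removed does not differ from the rest of the arm, and equal shifts in both arms cancel. If participants left the analysis entirely, power at f = 0.38 would be 0.805 with 5% lost (N = 57), 0.782 with 10% (N = 54), 0.758 with 15% (N = 51) and 0.732 with 20% (N = 48).

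**The case against.** The strongest defence is that nothing in the article removes anyone from the analysis. Exclusion criteria are checked at T0, no PANSS is scheduled during the treatment days, and the clause may be a loosely worded entry criterion or a safeguard for stopping stimulation. On either reading the ITT statement in section 2.5 governs, and detailed handling of withdrawals may sit in the full protocol. This stands in part. It is why the point is a conflict to reconcile and not a proven removal. It does not dispose of the wording, because the literal reading remains open and no sentence in the article closes it.

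A reader might also infer that the dropout rule takes randomised participants out: "A participant will be considered a dropout if they miss any of the intervention protocol sessions, resulting in a loss of four sessions" of iTBS. The article does not support that. Section 2.5 uses all data regardless of completion, and the only stated use of the dropout label is a descriptive comparison with completers. Nothing ends the assessment of participants who miss sessions. With four sessions a day, the sentence reads naturally as one missed treatment day.

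A reader might further infer that the two PANSS limits contradict each other. They do not do so outright: an item ceiling and a scale cap can both be required, and a patient can satisfy both. What is unclear is whether both apply at T0.

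It is also fair to say that the bias figures are hypothetical. The criterion concerns positive symptoms and the primary outcome concerns negative symptoms, and the article does not link the two by any stated amount. Nor is worsening necessarily hidden, since an adverse effects scale is completed each treatment day and PANSS is repeated at T1 and T2.

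**Conclusion.** The point holds for the exclusion clause. Taken literally, it excludes randomised participants on an event that treatment may influence, and this is not reconciled with T0 screening or with the ITT analysis of all participants. The comparison could be biased if removals differ by arm. The article neither states that data are deleted nor gives a rate for the event, so no size of bias can be established. The range of 0 to 0.11 SD rests on an assumed 0 to 3 removals in one arm of 30 and a BNSS up to 1 SD worse in those removed. The power range of 0.805 to 0.732 rests on an assumed 5% to 20% leaving the analysis altogether, which section 2.5 does not provide for.

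The unclear relation between the two PANSS limits is a secondary part of the same point. Its worked example depends on the assumption of seven items.

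**What to change.** Reconcile the exclusion criteria, the Procedures and section 2.5 in one edit:

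- State whether the clause is an eligibility criterion applied at T0 or a rule for stopping stimulation. That choice is the sponsor's clinical decision.
- In either case, state that a participant who meets it after allocation stays in the ITT set, is assessed at T1 and T2 as scheduled, and has the worsening recorded as a safety event.
- State how the PANSS scale limit (20 or above) and the item limit (4 or below) apply together, and at which time point.

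The cost is a few sentences of protocol text. The T1 and T2 visits are already scheduled, so the only added work is to keep assessing participants who might otherwise not have been followed.
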